### Sample and Eligibility Criteria

The sample consists of 439 caregiver-child dyads living in 3 cities in Azerbaijan: Baku, Sumgait, and Ganja. Caregivers and children must meet the eligibility criteria to participate and commit to study participation to be enrolled. Eligible children (1) are 7 to 12 years old at baseline, (2) have a history of institutionalization (for at least 1 month), and (3) have been reunited with a caregiver (biological parent or kin relative) within a year before the start of the study.

Eligible caregivers (1) are a biological parent or kin relative (eg, grandparent) who serves as the primary caregiver;, (2) reunified with the child before the study, and (3) are at least 18 years old at baseline. Children or caregivers with significant cognitive, behavioral, and/or mental health impairment (eg, severe developmental disorder) that may interfere with their ability to consent to, benefit from, or participate safely in the program are excluded from participation. More than 1 eligible child in a family may be enrolled in the study. Enrollment requires consent from the caregiver and assent from the child (see Multimedia Appendix 1 for sample consent and assent forms).

### Power Calculations

Power calculations were conducted using the G*Power software [18,19]. To account for the repeated-measures design, power estimates were modeled across a range of effect sizes at 2 assumed autocorrelation values (ρ). Analyses were performed for a 2-tailed test with a type 1 error rate of 0.05 and desired power of 0.80, assuming a final analyzed sample size of 360 child participants (180 participants per intervention type) after a projected 10% attrition from an initial planned sample of 400 child participants (200 participants per intervention type). The results indicate that for continuous outcomes, 80% power is achieved for effect sizes between 0.09 and 0.12. The study is sufficiently powered to detect small-to-medium effects [20] for continuous outcomes over the entire follow-up period. In the MOST design, the study is powered based on the intervention component with the smallest effect size—in this case, the family-strengthening component.

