Aim 1: To estimate the effects of intervention components on child mental health outcomes, differences in outcomes (eg, depression score) will be tested across 3 time points (baseline, 1 year, and 2 years), under an intent-to-treat basis, using linear mixed models. This approach accounts for the autocorrelation of observations nested within individuals over time. We will use logistic functions for binary outcomes (eg, mental health symptoms above the clinical cutoff), Poisson or negative binomial functions for count outcomes (eg, the number of aggressive behaviors), and linear functions for continuous variables (eg, self-esteem score). Statistical inference will be based on F-statistics and their associated *P* values for between-subject effects (the intervention assignment × time terms). To estimate the main effects for the 3 intervention components, we will determine if there is a difference in change across time using the baseline as the reference point (eg, 1 year vs baseline; 2 years vs baseline). We will also include 2-way interactions between components (eg, Family Strengthening by Economic Empowerment by Time interaction). Since we will use effect (–1, 1) coding rather than dummy (0, 1) coding, the power for tests of main effects and interactions will be identical for similarly sized effects. Covariates will include baseline attributes for outcome variables (eg, child’s age and gender, caregiver characteristics).Aim 2: To test which intervention component is mediated by hypothesized mediators, including (1) supportive parenting (eg, quality of child-parent relationships), (2) emotion regulation (eg, self-regulation), and (3) parental stress (eg, stress response). We will use a 2-step process [61] to test (1) a measurement model using confirmatory factor analysis that examines the relationships between the latent constructs and their indicator variables and (2) a structural model to test the hypothesized relationships between the latent mediating and outcome constructs and the intervention [62]. We will use the maximum likelihood method of parameter estimation with missing data. We will also conduct separate analyses to examine the effectiveness of intervention components in specific subgroups (eg, by gender).Aim 3: Qualitative analysis will be conducted in both Azerbaijani and English to explore barriers and facilitators to intervention participation and implementation. Bilingual investigators and 2 additional coders will independently review interview transcripts and conduct thematic analysis [63] and content analysis [64] using Dedoose [65]. Analyses will assess themes and concepts regarding participants’ and intervention facilitators’ perspectives on mental health needs, intervention engagement and acceptability, changes in family relationships and dynamics, and contextual and sociocultural factors influencing intervention delivery and outcomes.

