
In the data analysis, the primary outcomes include children’s mental health and socioemotional functioning. Secondary outcomes include cognitive and social processes associated with mental health, as well as functional outcomes related to academic performance and social functioning in the school setting. Specifically, primary mental health outcomes include child-reported depressive symptoms, posttraumatic stress symptoms, and self-esteem; caregiver- and teacher-reported ADHD symptoms and general socioemotional functioning such as internalizing and externalizing problems; and clinician-administered mental health outcomes among families randomized to the mental health services condition. Secondary outcomes include child cognitive functioning, assessed using WISC-V and CANTAB tasks; child-reported social support, particularly peer support; and teacher-reported grades and school behaviors. Mediating variables include caregiver-reported parenting practices, caregiver mental health, family functioning, coping strategies, social support, saving attitudes, and household economic well-being.

The main analyses focus on treatment effects at the 1-year and 2-year follow-ups, with the 1-year follow-up used to assess initial intervention effects and the 2-year follow-up used to assess the maintenance of those effects over time. Children from the same family will be accounted for using mixed-effects models, with random effects specified to adjust for the nonindependence of observations among children nested within the same family. Missing outcome data will be handled using maximum-likelihood estimation under a missing-at-random assumption, with sensitivity analyses using multiple imputation. To address the multiple testing issue, we will control the false discovery rate using the Benjamini-Hochberg procedure [66,67]. This approach was selected instead of Bonferroni correction because it limits false discoveries while avoiding the overly conservative loss of power associated with Bonferroni adjustment when multiple related hypotheses are tested.

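### The stated 80% power is per-comparison power at alpha 0.05, not the power of the Benjamini-Hochberg rule that the analysis will apply

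*Protocol article*

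**What the plan says.** Power Calculations sizes the trial on one test: "Analyses were performed for a 2-tailed test with a type 1 error rate of 0.05 and desired power of 0.80". The analysed sample is 360 children, 180 with and 180 without each component, "after a projected 10% attrition from an initial planned sample of 400 child participants". The result is that "80% power is achieved for effect sizes between 0.09 and 0.12", and the section concludes that power is sufficient for continuous outcomes. It adds that power is set on the component with the smallest effect, family strengthening.

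Analytical Strategy uses a different rule for declaring effects: "To address the multiple testing issue, we will control the false discovery rate using the Benjamini-Hochberg procedure". It prefers this to Bonferroni because Bonferroni loses more power. The tests to be covered are numerous. The "primary mental health outcomes include child-reported depressive symptoms, posttraumatic stress symptoms, and self-esteem; caregiver- and teacher-reported ADHD symptoms and general socioemotional functioning". Aim 1 estimates a main effect for each of the three components, with change from baseline to 1 year and to 2 years, and adds: "We will also include 2-way interactions between components".

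No section gives power under Benjamini-Hochberg. The Discussion concedes limited power only for smaller interaction effects and subgroup differences, which leaves the main-effect figure as stated.

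**The concern.** A single test at two-sided 0.05 rejects whenever P is at most 0.05. Benjamini-Hochberg at level q over M tests orders the P values and rejects up to the largest rank k whose P value is at most q × k / M. At q = 0.05 no test with P above 0.05 can be rejected, so single-test power is a ceiling, reached only when every other test in the family is also rejected. The article quotes the power of the first rule and will act on the second.

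This matters because the trial belongs to the optimization phase and is meant to identify the best package of components. A null result on an outcome looks more informative when read against 80% power than it is if the power of the rule was 55% or 60%. The exposure is largest for a component whose benefit is confined to one or two outcomes.

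**Working it through.** **Inputs from the article.** Two-sided alpha 0.05, power 0.80, 360 analysed from 400 planned (Power Calculations); three time points, three components and Benjamini-Hochberg control (Analytical Strategy); 439 children enrolled (Results). Primary scores available in all arms: depression, posttraumatic stress and self-esteem from the child (3), plus ADHD and socioemotional functioning, each from caregiver and teacher (2 × 2 = 4), making 7.

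**Assumptions, because the article does not give them.** q = 0.05, with 0.10 as a variation. Family of 7 tests (one component, one test per score) or 21 (7 × 3 components). Test statistics independent, or equally correlated at 0.4. Clustering of siblings is set aside.

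**Step 1: the plan's own figures.** 400 × 0.90 = 360, so the attrition arithmetic reproduces. The metric behind 0.09–0.12 and the two autocorrelations are not stated, so the range cannot be verified. It is attainable: for a two-group between-factor repeated-measures test in Cohen's f, the noncentrality is N·m·f² / (1 + (m − 1)ρ). With N = 360 and m = 3, power is 0.803 at f = 0.09, ρ = 0.05, and 0.794 at f = 0.12, ρ = 0.5. Both use unadjusted alpha 0.05.

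**Step 2: the planned effect on the z scale.** An effect with exactly 80% power at two-sided 0.05 shifts z by 1.960 + 0.842 = 2.80.

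**Step 3: floor from the first Benjamini-Hochberg step.** With 7 tests the smallest P value is compared with 0.05 / 7 = 0.0071, and power at that level is 0.54. With 21 tests it is 0.05 / 21 = 0.0024, and power is 0.41.

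**Step 4: simulated average power per truly affected outcome.** 20,000 to 40,000 runs per case, every true effect at shift 2.80, q = 0.05. Differences of about one point are simulation error.

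| Family | Effects real | Independent | Correlation 0.4 |
|---|---|---|---|
| 7 | 1 | 55% | 55% |
| 7 | 2 | 61% | 61% |
| 7 | 4 | 70% | 68% |
| 7 | 7 | 77% | 75% |
| 21 | 1 | 41% | 41% |
| 21 | 7 | 60% | 59% |
| 21 | 10 | 66% | 64% |
| 21 | 21 | 77% | 74% |

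A version using 2-df F tests agrees (42%, 61% and 77% for 21 tests with 1, 7 and 21 real).

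**Step 5: what moves the figures.**
- q = 0.10, 21 tests, independent: 51%, 72% and 86% with 1, 7 and 21 real.
- Larger effects elsewhere: 21 tests at q = 0.05, with the other two components' effects 1.5 times the planned size. Power per truly affected family-strengthening outcome is about 72% when 4 of 7 outcomes are affected for each component and about 79% when all 7 are.
- Achieved sample: 439 × 0.90 ≈ 395. The shift becomes 2.80 × √(395/360) = 2.94 and single-test power 0.835. At q = 0.05, 21 tests give 47%, 66% and 81% with 1, 7 and 21 real.

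**Step 6: chance of flagging at least one truly affected outcome.** Family of 7, q = 0.05, independent / correlation 0.4: 1 real, 55/55%; 2 real, 81/74%; 4 real, 97/88%; 7 real, over 99/about 94%.

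**The case against.** The article states its alpha openly, and sizing per comparison while controlling the false discovery rate in the analysis is common practice. That stands: a reader might infer that the 80% or the 0.09–0.12 range is miscalculated, but the range is attainable at alpha 0.05 and nothing in the article refutes it. What is missing is the label, since the section moves from this figure to a conclusion of sufficient power without saying that the figure precedes adjustment.

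The article fixes neither q nor the family, and an analysis plan not shown may do so. That also stands, and the absence is no fault in itself. It means that the size of the loss is not determined by the article, and that the rule is not necessarily stricter than the sizing test: at q = 0.10 with most effects real, power exceeds 80%. Even then, 80% is not the power of the rule. Larger families, splitting visits or adding interactions, would give lower figures, but the article does not commit to them.

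Setting every true effect at the planned size is pessimistic for a pooled family, because the plan expects family strengthening to have the smallest effect. Larger effects elsewhere recover much of the loss (Step 5), as does enrolment above 400 in part.

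Finally, a reader might infer that an effective component would often be dropped. The article does not support this. The figures are per outcome, no section says that one null outcome removes a component, and a component affecting several outcomes is usually flagged on at least one (Step 6).

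**Conclusion.** The point holds as a mismatch between the power statement and the decision rule, not as an arithmetic error. At q = 0.05 and with effects of exactly the planned size, the stated 80% corresponds to about 55–77% per truly affected outcome in a family of 7 and about 41–77% in a family of 21. The shortfall ranges from about 3 points (independent tests, all effects real) to 25–39 points (only one real). These figures depend on the assumed q, family, share of real effects and correlation. The practical exposure is a null on a single outcome, above all for a component with a narrow effect.

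**What to change.** In Power Calculations, label the 80% for effect sizes 0.09–0.12 as per-comparison power before false discovery rate control. State the Benjamini-Hochberg family and q, for example the seven common primary scores within one component. Give the power, or the minimum detectable effect at 80% power, under that rule over a stated range of true effects, using 439 less attrition. In the results paper, interpret null findings on single outcomes against the restated figure and their confidence intervals.

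The cost is a short simulation and a few sentences, with no further participants or data. The article reports that effect analyses are ongoing and that no intervention effects have been published, so the wording can be settled before results appear. It cannot change the sample, and the stated power will probably look less favourable.

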## Results

Recruitment was completed in 2023, and 2-year follow-up data collection was completed in 2025. The study enrolled 439 children and 305 of their caregiver participants from the 3 target sites, with 107/305 (35.1%) caregivers having more than 1 child participating in the study [68]. On average, children were 6.8 (SD 2.18) years old when they were placed in institutional care, with most placements occurring around the start of formal schooling, which institutional care facilities provide free of charge. The average duration of time in institutional care was close to 3 (mean 2.88, SD 2.39; range <1-12) years. Most participating caregivers are female 282/305 (92.5%) and predominantly mothers and grandmothers [68]. This sample exhibits economic instability, with 130/305 caregivers (42.6%) reporting that their family’s economic situation was bad or very bad [68,69].

Descriptive analyses of baseline data revealed substantial mental health needs among participating children [68]. At baseline, many children scored above clinical cutoffs for key mental health symptoms, including 221/425 (52%) for depressive symptoms, 156/429 (36.4%) for posttraumatic stress symptoms, and more than one-third for ADHD symptoms. Baseline analyses to date also suggest that economic instability and parental distress play important roles in child outcomes among this population [69]. Structural equation modeling analyses of baseline data identified an indirect pathway linking economic deprivation to child internalizing problems through parental distress and the family environment. Greater economic deprivation was associated with higher levels of parental distress (child-report model: *β*=.39, *P*<.001; parent-report model: *β*=.38, *P*<.001) which, in turn, was linked to a less supportive family environment (*β*=−.71, *P*<.001; *β*=−.69, *P*<.001, respectively). A more supportive family environment was associated with fewer child internalizing problems (*β*=−.29, *P*=.007; *β*=−.54, *P*<.001) [69], suggesting that parental distress and family functioning may represent important pathways through which economic hardship affects child mental health [69].

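### The power statement of 80% for effect sizes 0.09 to 0.12 names no metric, test or correlation, probably describes a different test from the planned one, and ignores sibling clustering

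*Protocol article*

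**What the plan says.** The Power Calculations section used G*Power for a repeated-measures design: "power estimates were modeled across a range of effect sizes at 2 assumed autocorrelation values (ρ"). On error rates it says: "Analyses were performed for a 2-tailed test with a type 1 error rate of 0.05 and desired power of 0.80". On sample size it continues: "assuming a final analyzed sample size of 360 child participants (180 participants per intervention type"), which is 400 less 10% attrition. The conclusion is: "The results indicate that for continuous outcomes, 80% power is achieved for effect sizes between 0.09 and 0.12". The section describes these as small-to-medium effects over the whole follow-up. It makes no allowance for children sharing a family.

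The Analytical Strategy (Aim 1) fits linear mixed models to three time points. It bases inference on F-tests "for between-subject effects (the intervention assignment × time terms"), with year 1 and year 2 each compared with baseline.

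On clustering, Sample and Eligibility Criteria states: "More than 1 eligible child in a family may be enrolled in the study". Randomization assigns families, in runs of five per condition. Results reports 439 children and 305 caregivers, with "107/305 (35.1%) caregivers having more than 1 child participating in the study". The Analytical Strategy includes random effects for children in the same family.

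**The concern.** A power figure can be used only if the reader knows the scale of the effect and the test it belongs to. Here neither is given, and the natural reading, a standardized mean difference, cannot be right for this sample size. The planned test is a component-by-time interaction, which the article labels a between-subject effect. In repeated-measures power software these are different options with different answers. The calculation also treats siblings as independent, although the analysis plan says they are not.

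The trial is meant to decide which components to keep. A reader who takes effects near 0.1 SD as reliably detectable would read too much into a null result for a component. The Discussion concedes limited power only for interactions and subgroups, so the claim for main effects stands unqualified.

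**Working it through.** **Inputs from the article.** N = 360 (180 per level of each component), two-sided alpha 0.05, power 0.80, m = 3 visits; 439 children in 305 families, 107 families with more than one child.

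**Assumptions, not in the article.** Correlation between visits (rho) 0.1 to 0.7; family ICC 0 to 0.5; family sizes as in step 4.

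**1. Reproducing the stated range.** For a two-group between-subjects test over m visits, the noncentrality is λ = f²·N·m / [1 + (m−1)·rho]. Solving for 80% power:
- rho = 0.1: f = 0.094 (λ = 0.094² × 1080 / 1.2 = 7.95)
- rho = 0.5: f = 0.121 (λ = 0.121² × 1080 / 2 = 7.91)

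These round to 0.09 and 0.12. The test compares levels on the mean of all three visits, including baseline, where randomization implies no component effect.

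**2. The planned interaction.** For two groups by time, λ = f²·N·m / (1−rho). Under sphericity f is at most 0.095 (rho = 0) and falls as rho rises, so 0.12 is out of reach for rho ≥ 0. Two other settings do give about the stated range:
- the 8-group-by-time omnibus test: 0.118 at rho 0.2, 0.093 at rho 0.5 (not a component test)
- the two-group interaction with the nonsphericity correction at its lower bound of 0.5: 0.121 at rho 0, 0.094 at rho 0.4

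**3. Reading the range as SD units.** Power at one visit is Φ(d·√(180/2) − 1.96):
- d = 0.09: Φ(0.854 − 1.96) = 13%
- d = 0.12: Φ(1.138 − 1.96) = 21%

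Read as Cohen's f, the range is d = 2f = 0.18 to 0.24 SD averaged over three visits. With no baseline difference and equal effects at both follow-ups, that is 1.5 times as much at each follow-up, 0.27 to 0.36 SD.

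**4. Family clustering.** The 107 multi-child families hold 439 − 198 = 241 children (55%). One split that fits is 198 families with one child, 80 with two and 27 with three (198 + 160 + 81 = 439). The size-weighted mean family size is (198×1 + 80×4 + 27×9)/439 = 761/439 = 1.73. The design effect is DE = 1 + 0.73·ICC; dividing λ in step 1 by DE gives:

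| Family ICC | DE | Power of the visit-averaged test (80% if independent) |
|---|---|---|
| 0.1 | 1.07 | 77% |
| 0.3 | 1.22 | 72% |
| 0.5 | 1.37 | 67% |

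**5. The planned contrast in SD units.** For change from baseline to one follow-up, the difference detectable with 80% power is 2.80·√[(4/N)·2(1−rho)·DE], where the ICC in DE is that of the change score. For N = 360:

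| rho | Independent | ICC 0.1 | ICC 0.3 | ICC 0.5 |
|---|---|---|---|---|
| 0.1 | 0.40 | 0.41 | 0.44 | 0.46 |
| 0.3 | 0.35 | 0.36 | 0.39 | 0.41 |
| 0.5 | 0.30 | 0.31 | 0.33 | 0.35 |
| 0.7 | 0.23 | 0.24 | 0.25 | 0.27 |

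With 439 × 0.9 ≈ 395 children these fall by about 5% (√(360/395) = 0.955). Baseline-adjusted estimation replaces 2(1−rho) by 1−rho² and, for independent children at N = 360, gives 0.29 at rho 0.1, 0.26 at rho 0.5 and 0.21 at rho 0.7.

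**The case against.** The strongest reply is that the figure is not a miscalculation. It reproduces, and the small-to-medium label fits Cohen's f reasonably well. The software option is inferred: step 2 shows that a component-by-time test with a nonsphericity correction can also give the range, and the full protocol may state the settings. This stands, so the mismatch with the planned test is likely rather than proven. It does not supply the missing metric, and no setting makes the range valid in SD units.

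Second, clustering is modest and handled in the analysis. The larger enrolment (395 against 360 after attrition, a ratio of 1.10) about offsets the design effect at ICC 0.1. That is fair at low ICC, but not at 0.3 or above. Modelling the clustering also does not correct a power figure that omitted it.

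Third, the article claims power over the whole follow-up, whereas step 5 takes one visit at a time. Averaging both follow-ups against baseline replaces 2(1−rho) by 1.5(1−rho) and gives 0.26 SD at rho 0.5 or 0.20 at rho 0.7 for independent children. This is better, but still well above 0.12.

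Some stronger readings are tempting and not supported:
- **That the trial is underpowered for the very effect it was sized on.** A reader might put the visit-averaged 0.24 SD straight into the follow-up contrast. If baseline shows no difference, the matching follow-up effect is 0.36 SD, which at rho 0.5 has about 93% power for independent children. At rho 0.1 the matching effect (3 × 0.094 = 0.28 SD) has about 51%. So whether there is a shortfall depends on a rho the article does not give.
- **That the design detects only effects up to 0.5 SD.** No assumption tried at alpha 0.05 reaches 0.5. A constant family effect cancels from change scores, so only the ICC of change, usually smaller, inflates that contrast.
- **That multiplicity control makes the figure far worse.** The article says "we will control the false discovery rate using the Benjamini-Hochberg procedure", but planning at 0.05 alongside this is common, and the article does not fix the number of tests, so no size can be put on it.
- **That treatment in groups of five adds a known loss.** Some loss is possible, but the article gives no ICC from which to compute it.

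**Conclusion.** The power statement is wrong as written: a specific figure is published on an unnamed scale, for an unnamed test, with siblings counted as independent. Two parts are firm. The range cannot be SD units (13% to 21% power at one visit), and family clustering is absent although the article's own allocation, enrolment and analysis all involve it. The loss for the visit-averaged test is from 80% to about 77%, 72% or 67% at family ICC 0.1, 0.3 or 0.5, given N = 360 and a size-weighted mean family size of 1.73. A third part is likely but not certain: that the figure belongs to a test averaged over baseline and both follow-ups rather than to the planned contrasts.

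For the planned change contrast at one follow-up, a defensible guide is roughly 0.25 to 0.45 SD. This rests on assumed rho (0.1 to 0.7) and ICC of change. Recruitment and follow-up are complete, so the sample size is not in question; what needs correcting is the claim about what it can detect.

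**What to change.** Restate Power Calculations for the component-by-time contrast that Aim 1 tests, and correct the between-subject label in the Analytical Strategy. Name the metric, the test, both rho values and the family ICC. Give the detectable difference in SD units with a family design effect, for 360 children and for about 395 (439 less 10%). Possible wording, with placeholders for the trial's own values:

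> With 360 analysed children (180 per level of each component) and two-sided alpha 0.05, the component contrast in change from baseline at [year 1 / year 2] has 80% power for a difference of [x] SD, assuming a between-visit correlation of [rho] and a family ICC of change of [ICC]. With 395 children the figure is [y] SD. These figures are before false discovery rate control.

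If the primary estimate is baseline-adjusted, or pools both follow-ups, give the figure for that estimate. Keep 0.09 to 0.12 only if it is labelled with its metric, test and rho. The values in the working are a guide, to be replaced by the trial's own estimates of rho and ICC.

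The cost is a short recalculation and a less favourable stated figure. No more participants or data are needed.
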